### Primary study outcome

*The primary outcome* of the study is the rate of complete abortion, when no signs of pregnancy or retention of POC is present, or upon a negative LSUP test, and no further treatment is needed for termination of the pregnancy, in both groups. Established classification of efficacy for medical abortion will be followed to determine the outcome of the abortion procedure
[22,35]. Hence the primary outcome is; efficacy of home-based assessment, measured as the rate of complete abortion, relative to routine follow up at two weeks after initiation of medical abortion. The failed abortion rate will be measured through number of surgical interventions, clinical administration of additional misoprostol or on-going pregnancies established upon clinical examination.

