### Sample size

The success rate of medical abortion is 95%
[31,32] resulting in a complication rate estimation of 5% in both groups. The primary outcome define the sample size estimation where the 5% non-inferiority margin (delta) establishes the non-inferiority of the home-based self-assessment following medical abortion as compared to the routine clinic follow-up. The delta margin is defined by the clinical assessment standpoint where a 5% difference does not have clinical importance. To proof the non-inferiority of the intervention at a significance level of α = 0,05 and a power of 80%, 596 women are needed. The lost to follow-up estimation of 20%, based on field-testing in the study area, resulted in a final sample size of 716 women. A two-sided 95% confidence interval (CI) (or a one-sided 97,5% CI) will determine the difference in percentage of women requiring surgical intervention from the two groups.

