#### Follow up of home-based assessment group on day 12–15

At the time of follow-up, the RA will record the outcome of the LSUP-test along with side effects and other complications as reported by the woman. The women have been informed to return to the clinic in case of a positive LSUP test. However, the RA will refer the women that have not yet returned by the time of the follow-up visit to the clinic. To understand whether women are capable of assessing their abortion outcome using and interpreting the LSUP-test by themselves, different questions in the research questionnaire have been included. This is to distinguish whether the RA assisted the woman to conduct the LSUP-test at the time of follow-up or whether the woman had done it and interpreted it herself in advance of the RA consultation. In addition to the LSUP-test result the following set of questions will be asked by the RA to screen for other complications as well as the woman’s capacity to assess any side-effects: Do you think your abortion is complete? Did you see expulsion of products? If you had any pregnancy symptoms before are they gone now? Did you bleed more than twice as much as a normal period after taking the pill? Do you still have heavy bleeding? Do you still have severe abdominal pain? Do you feel sick? Have you had fever? Do you feel weaker than usual or like your whole body are aching? If the answer is yes to any of these questions, the RA may choose to refer the woman to the clinic regardless of the result of the LSUP-test. Important to notice is that the pictorial instruction sheet as well as the instructions given in the clinic emphasize the side effects or danger signs requiring a clinical visit. Hence the role of the RA is not to assess the abortion outcome of the woman during the follow-up visit. Moreover, women are not obliged to follow the advise of the RA to return to the clinic. Women with a negative LSUP-test, assessed as complete abortion at the time of follow-up, will be censored out of the study. Women that present with a positive LSUP test but do not return to the clinic will be approached through phone calls or home visits to confirm their abortion outcome in retrospect. Clinical records will be monitored in case of any adverse events or additional procedures in relation to the abortion for up to one-month post abortion.

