#### Follow-up of clinic follow-up group on day 10–14

Women allocated to the clinic follow-up group will be treated according to the routine practice of each clinic. For the cause of the study the time of the follow-up visit has been standardized to 14 days after initiation of medical abortion, or within the range of 10–14 days. At the follow-up visit, a doctor will assess the outcome of the abortion including a pelvic examination if regarded as necessary. Subsequently, an RA will carry out the final interview in the clinic before the woman will be censored out of the study. Women returning to the clinic will be reimbursed for their travel expenses (INR 200), while women that do not return for clinical follow-up will be reminded to return to the clinic over phone, where possible.

All women

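### A negative test can settle the primary outcome, and negative home tests get no routine clinical check, so failures missed at home tend to favour non-inferiority

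*Protocol article*

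**What the plan says.** The Primary study outcome section defines complete abortion, for both groups, as "when no signs of pregnancy or retention of POC is present, or upon a negative LSUP test, and no further treatment is needed". The Definitions section has the same wording. Failure is to be measured through surgical interventions, additional misoprostol given clinically, or on-going pregnancy confirmed by clinical examination.

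In the home arm the woman performs and reads the LSUP test herself on day 10–14. A research assistant contacts her on day 12–15, records the result and asks screening questions, but is not there to judge the outcome. The section on follow-up of this group then says: "Women with a negative LSUP-test, assessed as complete abortion at the time of follow-up, will be censored out of the study". It adds: "Clinical records will be monitored in case of any adverse events or additional procedures", for up to one month.

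In the clinic arm, at day 10–14, "a doctor will assess the outcome of the abortion including a pelvic examination if regarded as necessary". Under Clinic follow-up group, clinical staff also carry out an LSUP test and ask the same screening questions. The woman leaves the study after the final interview at that visit. No one-month record check is written under this arm.

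The Randomisation procedure section says that the clinical procedure on days one and three is the same whatever the allocation.

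**The concern.** Because the abortion treatment is the same in both arms, the follow-up method can hardly change the true rate of complete abortion. What it can change is whether a failure is found. The Background and the Home-based assessment group section themselves present detection of on-going pregnancy as the reason for follow-up.

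A rate of observed complete abortion gives detection the wrong sign: a method that overlooks failures scores better. In the home arm the test being evaluated also supplies the outcome, and a false negative is not routinely checked. Tracing is uneven too. Women with a positive test who do not return are pursued to confirm the outcome, while women with a negative test are not.

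In a non-inferiority comparison, under-detection in the new arm moves the estimate towards the desired conclusion. The Discussion concedes limited ability to identify on-going pregnancy, but treats it as a matter of sample size and does not mention this direction of bias.

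**Working it through.** **Inputs from the Sample size section.** Failure is 5% per arm ("resulting in a complication rate estimation of 5% in both groups"), the margin is 5 percentage points ("5% non-inferiority margin (delta) establishes the non-inferiority of the home-based self-assessment"), and the size is set "at a significance level of α = 0,05 and a power of 80%, 596 women are needed". The interval is a two-sided 95% CI, so one-sided 0.025. The Discussion gives 298 evaluable women per arm.

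**The plan's own figure.** n per arm = 2 × 0.95 × 0.05 × (1.960 + 0.842)² / 0.05² = 298.26. Rounded down this is 298 per arm, or 596, as stated. Power at 298 per arm is 79.97%. The figure reproduces and is not in dispute.

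**Assumptions added here.** The protocol gives no share of failures missed by a self-read test. Let m be the share missed in the home arm, and let the clinic arm miss none.

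Observed home failure = true home failure × (1 − m)

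P(non-inferiority) = Φ( [0.05 − (p_home − p_clinic)] / SE − 1.960 )

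SE = √{[p_home(1 − p_home) + p_clinic(1 − p_clinic)] / 298}

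Here p_home and p_clinic are observed failure rates. Each result was checked by exact enumeration of the two binomial distributions with the same Wald limit.

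**Case A: home arm truly at the margin (10% v 5% failure).** Any declaration of non-inferiority is false. Example with m = 0.20: p_home = 0.08, SE = 0.02016, and (0.05 − 0.03)/0.02016 − 1.960 = −0.968, giving 16.7%.

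| Share missed at home | Observed home failure | Normal approximation | Exact |
|---|---|---|---|
| 0% | 10% | 2.5% | 2.9% |
| 10% | 9% | 6.9% | 7.7% |
| 20% | 8% | 16.7% | 17.9% |
| 30% | 7% | 33.9% | 35.1% |

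**Case B: equal true failure (5% v 5%).** Example with m = 0.25: p_home = 0.0375, SE = 0.01675, and (0.05 + 0.0125)/0.01675 − 1.960 = 1.77, giving 96.2%.

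| Share missed at home | Observed home failure | Normal approximation | Exact |
|---|---|---|---|
| 0% | 5% | 80.0% | 79.9% |
| 10% | 4.5% | 88.4% | 88.2% |
| 25% | 3.75% | 96.2% | 96.0% |

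**If the clinic also misses failures.** With 5% true failure in both arms, 20% missed in the clinic (observed 4%) and 25% missed at home (observed 3.75%), exact enumeration at 298 per arm gives 90.7% instead of 96.0%. What matters is the difference in detection between the arms.

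**The record check.** It is written only under the home arm. Read literally, late failures would be sought to one month at home and only to the day 10–14 visit in the clinic. That difference alone adds failures to the home arm and works against non-inferiority.

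**The case against.** The strongest reply is that the outcome is defined identically in both groups and that a negative test is not enough by itself, because no further treatment may be needed. A home-arm woman with a negative test who later has an evacuation can be scored a failure on the present wording. The clinic arm also has an LSUP test, and its pelvic examination is discretionary, so full clinic detection is not assured. In the home arm the research assistant asks about expulsion, pregnancy symptoms, bleeding, pain and fever, and may refer the woman whatever the test shows. Interim-visit forms, the woman's own report of care elsewhere and three-month tracing of those lost to follow-up apply to all women.

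All of this stands. It places the problem in who ascertains the outcome and how, and it makes the bias smaller. It does not close the gap. Referral is optional and women need not follow it. The interim-visit question reaches only to the follow-up contact, and the tracing is for women lost to follow-up. Nothing says that what the record check finds enters the primary outcome.

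A reader might also infer that the differing windows add to the advantage of the home arm. They do not; taken literally they pull the other way. In a condensed article, the position of one sentence is also weak evidence that the check is meant for the home arm only.

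**Conclusion.** The point holds as one of unequal ascertainment. Failures behind a false-negative home test have fewer routes to being counted than failures in the clinic arm, and this tends to favour non-inferiority. Only the direction is established. The sizes (about 3% rising to 8–35% false non-inferiority at the margin, and 80% rising to 88% or 96% with equal true failure) rest on assumed miss rates and full clinic detection, and they ignore what the safeguards recover.

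A reader might go further and say that the trial would declare a worse method effective. The documents do not support that. With the same treatment in both arms, a true failure rate twice as high at home is only illustrative. With equal true failure, a finding of non-inferiority in true completion would be correct, and the bias then inflates the chance of success without making the claim false. What is lost is the ability of the endpoint to show that home follow-up detects failures less well.

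This is a cheap improvement that should be made. It is not an error that invalidates the design.

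**What to change.** - Define primary failure identically in both arms: any surgical evacuation, additional misoprostol or continuing pregnancy, from randomisation to one month, from any source (clinic records, interim-visit forms, the woman's report, the planned tracing) and whatever the LSUP result. A negative test alone then no longer settles success.
- State that the one-month record check applies to both arms and that its findings enter the primary outcome.
- Report by arm the failures first found after the scheduled assessment, with exact 95% CIs.
- State as a limitation that failures which never reach care stay undetected, and that this favours the home arm. The new definition does not cure this.

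The cost is some wording and a little record work for the clinic arm. The outcome becomes final only at one month, and the failure rate may come out slightly above 5%. The 596 evaluable women stay unchanged if the 5% rate holds.

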### Secondary study outcome

*The secondary outcomes* include acceptability of the home-based assessment and the home use of misoprostol, when applicable, measured at the time of follow-up. To evaluate acceptability, we will ask women of their choice of method and means of follow-up in the event of a future abortion. Additional acceptability questions will regard women’s advice to a sister or a friend in need of an abortion. Finally, we will ask women with previous abortion experience to compare their previous experience with their current experience. For the purpose of efficacy of the intervention, we will evaluate recordings of the number of, and reasons for interim visits related to the medical abortion as well as side effects including infections, bleeding and pain. In addition, we aim to evaluate contraceptive uptake at 10–15 days after medical abortion along with previous use of contraception. Finally, the time consumed while travelling to and waiting in the clinic will be assessed as reported by the woman at the time of follow-up.

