##### Home-based assessment group

The intervention in this study consists of a home-based assessment carried out by the woman herself 10–14 days after an early medical abortion using an LSUP-test. The 10–14 day time frame is influenced by the sensitivity of the LSUP-test (1000 units/litre)
[35]. It has been established that the human chorionic gonadotropin (hCG) levels of women with a gestational age no more than nine weeks drops substantially at 10–12 days after a medical abortion. However using a high-sensitivity pregnancy test or conducting the follow-up too early would result in increased numbers of false positives
[36]. Waiting for four weeks to evaluate the abortion outcome may result in on-going pregnancies with gestation above 12 weeks. In this study setting, abortions are not as readily available after 12 weeks of gestation making an early detection of on-going pregnancy crucial. Women allocated to this group will receive an LSUP-test along with a pictorial instruction sheet (Figure 
1). The women will be followed-up by an RA contacting the women over phone or through a home-visit, 12–15 days after initiation of the medical abortion. This is to ensure that the woman had enough time to carry out the LSUP-test by herself on day 10–14 before the contact with the RA. If the woman is not found at home or cannot be reached over phone, two additional attempts will be made to contact the woman.

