#### Instructions for home-based assessment group

RAs will use a prototype of the LSUP-test to demonstrate how to use it along with the pictorial instruction sheet. Means of follow-up and date and time will be decided upon according to the woman’s preference. If the woman has a phone and is willing to receive a phone call, this will be the primary choice of follow-up. When women do not have access to a confidential phone, a home-visit will be suggested as an alternative. If the woman prefers neither they are advised to come back to the clinic for follow-up after having conducted the LSUP-test at home. These women will only meet with an RA at the time of follow-up – no clinical care will be offered unless the woman presents with complications or a positive LSUP-test, this will be recorded accordingly.

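### Travel and waiting time is reported at follow-up, which in the home arm comes before any clinic trip that the same contact triggers, so the two arms are measured over unequal windows

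*Protocol article*

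**What the plan says.** The outcome is given one sentence, at the end of Secondary study outcome: "the time consumed while travelling to and waiting in the clinic will be assessed as reported by the woman at the time of follow-up".

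Follow-up is a different event in each arm.

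- **Clinic arm** (Follow-up of clinic follow-up group on day 10–14): the doctor assesses the woman in the clinic, the RA then holds the final interview there, and the woman leaves the study.
- **Home arm** (Home-based assessment group): "The women will be followed-up by an RA contacting the women over phone or through a home-visit, 12–15 days after initiation of the medical abortion".

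The section on home-arm follow-up on day 12–15 describes how a home-arm woman may come to attend the clinic. Some attend on their own: "The women have been informed to return to the clinic in case of a positive LSUP test". For those with a positive test who have not attended, "the RA will refer the women that have not yet returned by the time of the follow-up visit to the clinic". Symptom answers can also lead to referral: "the RA may choose to refer the woman to the clinic regardless of the result of the LSUP-test".

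A woman who wants neither a call nor a visit has a further route (Instructions for home-based assessment group): "they are advised to come back to the clinic for follow-up after having conducted the LSUP-test at home". She then sees only the RA, unless she has complications or a positive test.

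**The concern.** The question is put once in each arm, but at different points relative to the clinic trip. In the clinic arm the assessing trip has been made when the woman answers. In the home arm, a trip prompted by the RA's referral has not. Those trips belong to the time cost of home assessment, since they are how a suspected failure or complication reaches a clinician.

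Fewer required visits are part of the case for the intervention (Discussion), and the Adaptation phase section reports transport, lost income and lack of time as reasons for not returning. The Data analysis section compares the groups and assigns numerical variables to Student's t-test, so an unequal window would pass straight into a reported difference between arms.

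**Working it through.** The article states no figure for clinic time, so there is nothing to reproduce. The check has two parts.

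**1. Is a post-referral trip timed at any later step?**

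| Step described | Section | Covers a trip made after the RA contact? | Mentions time? |
|---|---|---|---|
| Interim visit form | Additional procedures, extra visits or lost to follow-up | No: for women returning before scheduled follow-up | No |
| Question on interim visits | Same | No: asked at follow-up | No |
| Re-contact of test-positive women who do not return: "will be approached through phone calls or home visits to confirm their abortion outcome in retrospect" | Home-arm follow-up, day 12–15 | Possibly, but its purpose is abortion outcome | No |
| Record monitoring to one month | Same | Yes, for adverse events and procedures | No |
| Tracing of lost women within three months | Additional procedures, extra visits or lost to follow-up | Possibly, but its purpose is abortion outcome | No |

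For many women the contact is also the last one: "Women with a negative LSUP-test, assessed as complete abortion at the time of follow-up, will be censored out of the study". No described step times the trip.

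**2. How large could the effect be?**

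Inputs:
- *T*: time for one clinic trip, assumed equal in both arms, with one assessing trip per clinic-arm woman.
- *f*: share of home-arm women who make a clinic trip. The only anchor is the 5% failure rate in Sample size. Other values are assumptions.
- *s*: share of those trips made before the RA contact, and so reportable at it. Not given, hence varied.
- 298 evaluable women per group (Discussion).

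Formulas:
- True saving per woman = T − fT = T(1 − f)
- Recorded saving = T − fsT = T(1 − fs)
- Relative overstatement = [(1 − fs) − (1 − f)]/(1 − f) = f(1 − s)/(1 − f)

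At f = 5%:
- s = 0: 0.05/0.95 = 5.3%; untimed trips 298 × 0.05 = 14.9, about 15 women.
- s = 0.5: 0.025/0.95 = 2.6%; untimed trips 298 × 0.025 = 7.45, about 7 women.

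| f | s = 0 | s = 0.5 | s = 0.8 |
|---|---|---|---|
| 2% | 2.0% | 1.0% | 0.4% |
| 5% | 5.3% | 2.6% | 1.1% |
| 10% | 11.1% | 5.6% | 2.2% |
| 20% | 25.0% | 12.5% | 5.0% |

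The rows for 2%, 10% and 20% have no source in the article. They show only how the result moves.

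**Offsets.** Let *c* be the share of clinic-arm women with a trip after their interview (also untimed), and *q* the share of home-arm women whose attendance is only to meet the RA and is counted as clinic time. Then:

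- True saving = T(1 + c − f)
- Recorded saving = T(1 − fs − q)
- Recorded minus true = T[f(1 − s) − c − q]

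At f = 5% and s = 0 the sign reverses once c + q exceeds 5%; at s = 0.5, once it exceeds 2.5%. Neither c nor q is given.

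**The case against.** Several counter-arguments have force.

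- **The forms are not shown.** The questionnaire, interim visit form and study manual are outside the article, and a time item may sit on one of them. A reader might infer that referral trips are never timed. The article supports only that no later timing is described. The point stands because the article does fix the moment of report, and that moment falls before these trips.
- **Many trips may come earlier.** Women are told to return on their own after a positive test, and a trip made before the contact can be reported at it. Referral is also not binding. Both reduce the untimed share, so 5.3% is the upper end at a 5% trip rate and not a central estimate. Symptom referral works the other way, because it is not limited to failed abortions.
- **The clinic arm is incomplete too.** Its women leave the study after the interview, so later trips are missed there as well. This is a partial offset, since additional procedures can be given at the follow-up visit itself.
- **RA-only attendances should be few and can be identified.** Agreeing to follow-up by phone or home visit is an inclusion criterion, although the recruitment and ethics sections also allow the clinic. The trial registry records the means and location of follow-up, so these attendances can be separated at analysis. They weaken the measure only if they are counted without distinction.
- **The outcome is secondary and self-reported.** This limits the importance but does not remove the unequal window.

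**Conclusion.** The point holds as an unequal measurement window in a secondary outcome. As worded, the clinic arm's time includes the assessing trip, while the home arm's time leaves out any trip that follows a referral made at the day 12–15 contact. Taken alone, this component makes home assessment look more time-saving than it is, by about 2.6% to 5.3% if trips take equal time, 5% of home-arm women need one, and half to all of those trips follow the contact. The figure is higher if symptom referrals are common, and lower if women return earlier or do not act on the referral. The article does not determine it.

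A reader might go further and infer that the reported time saving is overstated overall. The article does not support that: clinic-arm trips after the interview and RA-only attendances pull the other way, and their shares are unknown. Nor does it follow that the difference says nothing about the time cost of either scheme. At a 5% trip rate about 95% of home-arm women have no trip to miss, and the scheduled clinic-arm trip is captured.

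The primary outcome is unaffected. Priority is minor to moderate.

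**What to change.** 1. In Secondary study outcome, define the measure as total travel and waiting time for all abortion-related clinic attendances after day 3 up to the existing one-month record check, in both arms. That record check is described under the home arm's heading, so state that the window applies to both. Starting after day 3 is reasonable because the procedures on days one and three do not depend on allocation.
2. Record travel and waiting time at any study-clinic attendance after the home-arm contact or the clinic-arm interview.
3. Use the location of follow-up, already held in the trial registry, to report attendances made only to meet the RA separately from the rest.

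The cost is two extra form fields and a sentence or two in the outcome definition. Referral, treatment and the primary outcome do not change. The remaining weakness is that later visits to providers outside the study sites would still be missed, and the report should say so.
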